### IV. Research Methods

**Overall strategy.** We will conduct a randomized controlled trial in African American and white patients with uncontrolled hypertension, comparing a values affirmation intervention to a control exercise in three healthcare systems. The primary outcome will be change in medication adherence with secondary outcomes of change in blood pressure, time under blood pressure control and treatment intensification. We will explore the mechanistic effects of the intervention and assess the suitability of the intervention for more widespread dissemination.

- A. Outcome Measure(s):** The primary outcome measure is medication adherence comparing adherence before and after the intervention. The secondary outcome measures are systolic blood pressure (comparing blood pressure at the index visit to blood pressure at 6-month follow-up), time under blood pressure control and treatment intensification.

**Primary Outcome: Medication adherence.** We plan to measure medication adherence in three ways. First, we will assess adherence using electronic pharmacy records as in our pilot study. Computerized pharmacy records have been used in a wide array of studies to assess medication adherence and correlate with other adherence measures such as electronic adherence monitors, self-report, and pill counts, and with treatment outcomes such as BP control. The measure of interest for the proposed study will be a summary measure of adherence which assesses the proportion of days covered (PDC) over the period of observation for which a patient obtains antihypertensive medications. Adherence will be calculated for each antihypertensive drug in the regimen and combined across drugs into a summary measure of adherence for the entire drug regimen using the method developed by [name] et al. We will calculate prior adherence using data from 12 months prior to the index visit to calculate change in adherence compared with the six months after the index visit. The investigator team has used this method to measure adherence in prior studies.

Second, because some patients will have only one refill opportunity (90-day supplies) over the 6-month follow-up period, we will also collect self-reported adherence at baseline, 3 and 6-months using the validated Voils instrument. The measure has three questions that address the *extent* of non-adherence over the previous 7 days.

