### C. Study Design and Research Methods

[figure not shown]

**Overview:** The study design was developed in consultation with providers at the study sites to ensure feasibility of implementation in routine clinical practice. All primary care providers (PCP) at the participating clinics will be invited to complete a baseline survey regarding past disparities training and racial attitudes; patient participation will be independent of whether their PCP

participates. We will enroll self-identified African American and white patients with uncontrolled hypertension who are eligible and consent for the study. Our primary outcome is medication adherence that will be measured in three ways: 1) pharmacy fills, 2) self-report, and 3) pill counts. At the index visit, before they see their PCP, participants will have their blood pressure recorded and will complete a survey which includes a validated self-report measure of adherence (see Table 1 for survey contents). We will also query the EHR for baseline adherence based on prior 12-months pharmacy fills. Participants will be randomized to the values affirmation or control intervention tasks and they will complete the assigned task before seeing their PCP as scheduled. Following the visit, patients will complete a brief survey. Participants will return at 3-months and 6-months for in-person follow-up visits that will include assessment of adherence, blood pressure measurement and completion of surveys. Participants will be asked to bring all antihypertensive medications to each follow-up visit, and fill date and number of pills in the bottle will be recorded. Adherence will be calculated for each antihypertensive drug in the regimen and combined across drugs into a summary measure of adherence for the entire drug regimen. Secondary outcomes include blood pressure, time under blood pressure control, and appropriate treatment intensification. Throughout the study, we will evaluate the intervention for widespread dissemination based on the RE-AIM framework.

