#### **Data collection and management**

Data warehouses (DW) - DH and the KP health systems maintain extensive patient data in a series of standardized data warehouses that are available for research and evaluation

applications. DH's data warehouse includes integrated administrative and clinical data as well as disease management registries for conditions such as hypertension and diabetes. Within KP, the Virtual Data Warehouse (VDW) standardizes clinical, utilization and demographic research data into a common structure shared by all members of the Kaiser Permanente health system. The VDW facilitates collaborative efforts with other KP sites by enabling a single analytic script to be used to extract and process data at each research site, significantly reducing the effort and time required to conduct multi-site studies. The data collected and maintained in both systems includes: membership and demographic information, clinical office visit procedures (CPT-4 codes) and diagnoses (ICD-9 codes), pharmacy dispensing, radiology procedures, lab tests and results, patient office visit registration, hospital inpatient and outpatient data, and health care provider information. Historical data in both systems go back to 2004, with some data available as far back as 1995.

Our research team has successfully standardized data definitions from DH and KP data warehouses on prior hypertension studies. As part of this prior work, data elements and data dictionaries relevant to hypertension (i.e. blood pressures, antihypertensive medication names, classes, doses) have been created which specify a common format for each of the elements—variable name, variable label, extended definition, code values, and value labels. Local site programmers have mapped the data elements from their health systems data onto this standardized set of variable definitions, names, and codes, as well as onto standardized SAS file formats. This common structure of the files enables a SAS analyst at one site to write one program to extract and/or analyze data at all participating sites. The program will be emailed to programmers at the sites to run against their own data warehouse files and the resultant de-identified data are transferred to the analytic site via a secure encrypted Web site.

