**Level 1 model.** Repeated measures within each patient will be modeled as a growth curve model (shown here) or repeated measures. Time will be coded 0 for baseline and days since baseline for all post-baseline measures. The outcome for patient  $i$  measured at time  $t$  in practice  $j$  is  $Y_{tij}$

$$Y_{tij} = \pi_{0ij} + \pi_{1ij}(\text{time})_{ij} + \varepsilon_{tij}$$

where  $\pi_{0ij}$  is the individual status at time 0,  $\pi_{1ij}$  is the linear growth rate for patient  $ij$ , and  $\varepsilon_{tij}$  is the term that represents the random deviation of observation  $t$  within patient  $ij$  from the predicted value.

**Level 2 model.** The patient level models specify the relationship between the patient-level coefficients and the coefficients in the Level 1 model. Intervention status will be coded 1, if intervention, 0, if control. Race (AA) will be coded 1, if African American; 0, if white. Interaction terms will be included to estimate differential intervention effects for AA vs white. Fixed patient-level covariates (not shown) will be included at this level.

$$\pi_{0i} = \beta_{00} + \beta_{01}$$

(Interv) +  $\beta_{02}$  (AA) +  $\beta_{03}$  (Interv x AA) +  $r_{0i}$

$$\pi_{1i} = \beta_{10} + \beta_{11}(\text{Interv}) + \beta_{12}(\text{AA}) + \beta_{13}(\text{Interv} \times \text{AA}) + r_{1i}$$

where  $\beta_{00j}$  represents the initial status of white, control patients within clinician  $j$ ,  $\beta_{01}$ ,  $\beta_{02}$ , and  $\beta_{03}$  represent baseline differences by intervention status and race.  $\beta_{10j}$  represents the linear growth rate for white control patients within clinician  $j$ ,  $\beta_{11}$  represents the difference in slope for white intervention vs controls,  $\beta_{12}$  represents the difference in slope for AA vs white control patients, and  $\beta_{13}$  represents the differential intervention effect for AA vs white patients within clinician  $j$ . The  $r$ 's are patient-level random effects.

**Level 3 model.** The provider level models specify the relationship between the provider-level predictors and the coefficients in the Level 2 model.

$$\beta_{00j} = \gamma_{000} + u_{00j}, \quad \beta_{01} = \gamma_{010}, \quad \beta_{02} = \gamma_{020}, \quad \beta_{03} = \gamma_{030}$$

$$\beta_{10j} = \gamma_{100}, \quad \beta_{11j} = \gamma_{110}, \quad \beta_{12j} = \gamma_{120}, \quad \beta_{13j} = \gamma_{130},$$

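### Baseline refill adherence appears to be cut off at 12 months of fills, and days of supply in hand at the index visit is not a listed covariate; correcting both gains a little precision, most for patients on 90-day supplies.

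*Protocol*

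**What the plan says.** Protocol section IV.A defines the refill measure as one that "assesses the proportion of days covered (PDC) over the period of observation for which a patient obtains antihypertensive medications", calculated per drug and "combined across drugs into a summary measure of adherence for the entire drug regimen using the method developed by" a cited source. Baseline will "calculate prior adherence using data from 12 months prior to the index visit", to give "change in adherence compared with the six months after the index visit". The Overview in section IV.C describes the extraction: "We will also query the EHR for baseline adherence based on prior 12-months pharmacy fills". Section IV.A also concedes the problem with long supplies, "because some patients will have only one refill opportunity (90-day supplies) over the 6-month follow-up period, we will also collect self-reported adherence", and adds pill counts as a further check.

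In section IV.F, baseline adherence is the time-0 value of the outcome in a growth model. Of the Level 2 model it says "Fixed patient-level covariates (not shown) will be included at this level". The covariates in Table 3 are antihypertensive medications, comorbid conditions, risk factors, socio-demographic factors and insurance payer. On the data warehouses, the data management section states "Historical data in both systems go back to 2004".

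**The concern.** A refill measure over a fixed window depends on the drug the patient already holds when the window opens. With 30-day fills that is at most a month. With 90-day fills it can be half of a six-month window.

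Two things follow. If the baseline query returns only fills dated inside the 12 months, no scoring rule can credit the opening supply, because it is not in the data. And supply in hand at the index visit helps determine six-month coverage, yet the exercise cannot alter it. It is therefore a natural pre-randomisation covariate, and the plan does not name it. What is at stake is precision in the outcome on which the trial is sized.

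**Working it through.** **The plan's own figure.** With a standardised difference of 0.26, two-sided alpha 0.05 and 80% power, n per cell = 2 × (1.96 + 0.84)² / 0.26², which gives 233 with unrounded quantiles. At the planned 240 per cell, power is 0.81. Enrolment is 960 / 0.85 = 1,130 to the nearest ten. The implied SD is 4.7 / 0.26 = 18.1 points. The stated sample size reproduces.

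**Baseline window, full adherence.** Assume one drug with supply in hand at day -365 uniform on 0 to S days, and score those days as uncovered. Coverage is (365 - days in hand) / 365.
- S = 90: range 275/365 = 75.3% to 100%; mean (365 - 45)/365 = 87.7%; SD (90/√12)/365 = 7.1 points.
- S = 30: mean (365 - 15)/365 = 95.9%; SD (30/√12)/365 = 2.4 points.
- With opening supply credited: 100% in both cases, SD 0.

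If scoring starts at the first fill inside the window, this shortfall disappears, but any genuine gap before that fill is dropped.

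**Baseline window, 80% adherence.** With regular refill cycles the mean is 0.80 × (1 - S/(2 × 365)).
- S = 90: 0.80 × (1 - 45/365) = 70.1%.
- S = 30: 0.80 × (1 - 15/365) = 76.7%.

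Equal true adherence thus reads 6.6 points apart under that scoring rule.

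**Days in hand as a covariate.** Simulation assumptions: one drug; refill after the supply runs out; exponential gaps; patient mean gaps that vary between patients and average 20-45% of the supply; 365- and 182-day windows; opening supply credited in both. Average coverage is close to the pilot's 74-83%. Adding days in hand at the index visit reduces residual variance as follows:
- change from baseline, 90-day fills: about 4-6%;
- change from baseline, 30-day fills: about 1-2%;
- six-month coverage regressed on baseline, 90-day fills: about 7-10%.

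The first two are the relevant figures, since the protocol models baseline as an outcome at time 0 and not as a covariate.

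**What this is worth.** A 4-6% cut in variance is a 2-3% cut in SD (1 - √0.96 = 2.0%; 1 - √0.94 = 3.0%). If the same proportion applied to the planning variance and every patient were on 90-day fills, 240 per cell would work like 240/0.96 = 250 to 240/0.94 = 255. The protocol gives the 90-day share only as some patients, so the trial-wide gain lies between the 30-day and 90-day figures.

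**The case against.** The strongest reply is that the protocol never says opening supply is disregarded. Section IV.A hands the calculation to a cited method that cannot be seen here, and carry-in handling could properly sit in an analysis plan. That stands. A reader might infer from the sentence on 90-day supplies that the refill measure ignores drug in hand, but that sentence only explains why self-report was added. The pilot does not support the inference either. If supply in hand were ignored over a fixed 182-day window, a fully adherent patient on 90-day fills would average (182 - 45)/182 = 75.3%, against pilot post-visit means of 81-83%. This is not decisive, because the pilot's supply lengths are not given.

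Three other stronger readings also fail.
- **A large precision gain.** If only fills after the index visit count, days in hand removes 25-47% of residual variance on 90-day fills. But that rule gives simulated six-month means of about 53-64%, far from the pilot's.
- **A wrong sample size.** The planning SD comes from a pilot that also used pharmacy records, so it may already contain this noise.
- **A biased comparison by race (additional analysis 6).** That needs days' supply to differ by race, which the protocol does not say, and its covariates already include medication use.

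It can also be said that the Level 2 covariates are left open and that days in hand could be derived from the medication data in Table 3. That is true, but neither commits the trial to using it.

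Finally, crediting opening supply in the six-month outcome adds days the exercise cannot affect and may dilute the effect. That is a fair caution about scoring the outcome. It does not touch the baseline window, which lies wholly before randomisation, or a covariate, which leaves the outcome as it is.

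**Conclusion.** The point holds in a limited form. As worded, the baseline query stops at 12 months of fills, so supply carried into that window appears to be missing although the warehouses hold it. If the Overview meant only the scoring window, one sentence would settle this. Separately, a useful pre-randomisation predictor of the primary outcome is not listed.

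Randomisation is by patient, so neither matter biases the comparison of arms. The benefit is modest: about 4-6% less residual variance of change on 90-day fills, 1-2% on 30-day fills, and something between the two across the trial. These sizes rest on the simulation assumptions given above, with one drug per patient and opening supply credited. The case for the change is that it costs very little, not that the present plan is unsound.

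**What to change.** 1. In section IV.A and the Overview in IV.C, state that fills are pulled from about 90 days before the 12-month baseline window opens, so that supply carried into that window can be credited.
2. In the Level 2 model, add days of antihypertensive supply in hand at the index visit, averaged over drugs, as a patient-level covariate. Enter it in the slope equation as well as the intercept; in the intercept alone it would not adjust change. List it among the covariates in Table 3.

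The cost is a slightly wider warehouse query and one more baseline covariate, with no added patient contact. For patients who use outside pharmacies, the request covers about three more months, so the look-back should be fixed before those requests are made.

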#### **Secondary Outcomes:**

**Blood pressure.** The research assistant will measure baseline, 3- and 6-month blood pressures according to guideline recommendations. To account for possible loss to follow-up, we will secondarily use the last blood pressure recorded in the EHR during the six-month post-enrollment period.

**Time Under Control** – will be defined as the proportion of time over the 12-months of follow-up with a BP  $\leq$  140/90 mmHg. Of note, BP control definitions will be modified if hypertension guidelines change during the study period. All BPs obtained during non-urgent clinic visits over the follow-up period will be included.

**Treatment Intensification** – Appropriate treatment intensification is another significant contributor to uncontrolled BP. Using a standard scoring method, appropriate treatment intensification will be calculated by subtracting the number of expected intensifications (number of visits after enrollment with a BP  $\geq$  140/90 mm Hg) from the number of observed intensifications (either an increase in dose or addition of a new medication class), and then dividing this difference by the number of office visits over the 12 months. Our group has previously measured treatment intensification using this approach.

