a PCP. Potential participants will be told the research is being done to assess adherence to hypertensive medications and to evaluate how a writing exercise about values might affect blood pressure. If they express interest in the study, they will be asked to arrive approximately one hour prior to the visit in order to review study procedures and provide informed consent. (see Patient Informed Consent) Those who decide to participate will have their blood pressure measured by the research coordinator using guideline-recommended procedures. Next, participants will be given a pre-randomized, consecutively numbered packet – to ensure the research coordinator is blind to the condition - containing the study materials. Packets will contain either an intervention or control version of the values affirmation exercise. To ensure balanced randomization by race at each site, there will be a pre-randomized series of packets for participants who self-identify as white and another pre-randomized series for those who self-identify as African American. Additional surveys will include a baseline demographics questionnaire, a measure of past experiences of discrimination, and a self-reported adherence (Voils) measure. (Table 1) Where patients feel comfortable using a tablet device, surveys will be administered and data will be collected on the tablet via an online survey format and stored in REDCap. If they do not feel comfortable with this format, all surveys will be administered on paper only. The values affirmation exercise will always be administered on paper, and the research assistant will provide instruction and remain available, but the patient will complete the exercise on their own, at their own pace. In our pilot work, patients completed all study materials in ~30 minutes. Next, patients will undergo routine check-in procedures, which includes blood pressure measurement at all sites, and complete the scheduled visit with their provider.

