#### **G. Summarize Knowledge to be Gained:**

Potential benefits of the proposed research to the subjects and others: Benefit from participating in the research cannot be claimed. If, however, the intervention being studied is effective, subjects randomized to the experimental group may experience improvements in blood pressure control and other parameters dependent on uptake of self-management skills. Given the magnitude of the problem of race-based health disparities, the potential of the proposed intervention to reduce these disparities, and the minimal risk to subjects, we are of the opinion that the risk-benefit ratio for this study is favorable.

Importance of the knowledge to be gained: Our preliminary data suggest the intervention will be effective. The current study is designed to generate knowledge that will justify widespread adoption if effectiveness is demonstrated. Because virtually no interventions to improve relationships between physicians and minority patients have been reported, a positive result of this study might have widespread clinical applicability. We also seek data on the potential for this social psychology intervention to have direct effect on blood pressure.

**IN SUMMARY**, our proposed study moves beyond documentation of race-based health disparities and towards an effective intervention. We focus on a medical condition – hypertension – that is arguably the single greatest contributor to mortality disparities for African

Americans. Our pilot data suggest a values-affirmation intervention improves patient-provider communication, which in turn improves subsequent medication adherence. Our pilot studies, however, leave gaps in knowledge that we propose to answer to determine the effectiveness of using values affirmation as a means of reducing racial disparities in health care. If successful, this study will be the first to provide evidence for a low-resource intervention that has the potential to substantially reduce healthcare disparities across a wide range of health care conditions and populations.

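### The EHR fallback for 6-month blood pressure has no earliest date and no visit-type limit, so an index-day or other early reading can stand in for the 6-month value in that supportive analysis

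*Protocol*

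**What the plan says.** Protocol section IV.A (Outcome Measures) defines the blood pressure outcome as systolic pressure at the index visit compared with systolic pressure at 6-month follow-up. Under Secondary Outcomes, the research assistant measures pressure at baseline, 3 and 6 months. A back-up source is then added: "To account for possible loss to follow-up", "we will secondarily use the last blood pressure recorded in the EHR during the six-month post-enrollment period". The rule gives no earliest date, no window around month 6, no exclusion of the index day and no restriction on visit type.

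The next outcome in the same section, time under control, does carry a visit-type restriction: "All BPs obtained during non-urgent clinic visits over the follow-up period will be included".

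Section IV.B (Patient recruitment and procedures) sets the order of events on the index day. After consent, "Those who decide to participate will have their blood pressure measured by the research coordinator using guideline-recommended procedures". The packet with the exercise and surveys follows, and "In our pilot work, patients completed all study materials in ~30 minutes". After that, "patients will undergo routine check-in procedures, which includes blood pressure measurement at all sites", and then the provider visit. The same section states that each site's EHR holds vital signs.

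**The concern.** The fallback exists for patients who do not return. Among them, those with no later clinic contact are the ones for whom the check-in reading on the index day may be the last EHR reading after enrolment. For these patients the analysis would compare two readings from the same visit and label the second one 6 months. The same gap lets a reading from the first weeks, or from an urgent visit, count as the 6-month value.

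If such readings carry no 6-month effect, they pull the estimated difference towards zero. The supportive analysis could then disagree with the visit-based analysis because of the data rule, not because of anything that happened to patients. Its purpose is to show whether the blood pressure result is robust to loss to follow-up, and the rule weakens it most in the patients it was added for.

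**Working it through.** **Reading the rule against the visit sequence.**

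1. The rule takes the last EHR reading in the six months after enrolment (IV.A).
2. A routine reading is taken at all sites on the index day, after consent and after the exercise (IV.B).
3. Each site's EHR holds vital signs (IV.B), so that reading is presumably stored there. This is an inference.
4. If the post-enrolment period begins at consent or randomisation, the reading falls inside it. The protocol does not define the start.
5. With no later EHR reading, it is the last one, and nothing elsewhere in the protocol narrows the rule. If the index day is excluded, step 4 fails for that reading, but a reading from the following days or weeks still qualifies.

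**The protocol's own figures (IV.F).** Inputs: effect size 0.26 SD between two cells, 240 per cell, two-sided alpha 0.05, 80% power, 15% attrition, 1,130 enrolled, detectable systolic difference 4.7 mmHg.

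- n per cell = 2(1.960 + 0.842)² / 0.26² = 232.2, so 233. The planned 240 gives about 81% power, consistent with the stated 80%.
- 960 / (1 − 0.15) = 1,129.4, so 1,130, as stated. Per cell, 1,130 / 4 = 282.5.
- The SD for systolic pressure is not stated. Equating 4.7 mmHg with 0.26 SD gives 4.7 / 0.26 = 18.1 mmHg.

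**Illustration.** Let f be the share of patients whose 6-month value is replaced by a reading that carries no 6-month effect. The protocol does not give f; 5%, 10% and 15% are assumptions.

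- Using the substituted readings: difference = 4.7 × (1 − f), effect size = 0.26 × (1 − f), n = 282.5 per cell.
- Treating the same patients as missing: effect size = 0.26, n = 282.5 × (1 − f) per cell.

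Two-sample t-test power:

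| f | Expected difference (mmHg) | Effect size | Power, readings substituted | n per cell if missing | Power, treated as missing | Cost of the rule (points) |
|---|---|---|---|---|---|---|
| 5% | 4.47 | 0.247 | 83.4% | 268.4 | 85.2% | 1.8 |
| 10% | 4.23 | 0.234 | 79.3% | 254.3 | 83.3% | 4.0 |
| 15% | 4.00 | 0.221 | 74.6% | 240.1 | 81.1% | 6.5 |

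With an SD of 18.4 mmHg instead (the value at which 240 per cell gives exactly 80% power for 4.7 mmHg, by normal approximation), the pairs are 82% and 84%, 78% and 82%, 73% and 80%. The cost of the rule is nearly the same.

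**The case against.** **The effect is limited to a back-up analysis.** This stands. The EHR value is used only secondarily. The blood pressure analysis described in IV.F is a mixed-effects repeated measures model on index and follow-up visits, with methods that use all available data under ignorable missingness. IV.F also concedes that the trial is likely underpowered for systolic pressure through adherence change alone.

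**The rule need not be read as including the index day.** This stands in part. The outcome definition places the index visit on the baseline side of the comparison, and treatment intensification counts visits after enrolment. A post-enrolment period that starts after the index visit is a fair reading. It would remove the check-in reading, but not other early or urgent-visit readings.

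**Detail may sit elsewhere.** IV.D says that a study protocol manual will describe each data element and its acceptable source, and the SAP is not shown. Either could add a window. But the protocol does not leave this rule open: it states the rule together with its only time limit, and a later document that followed it would inherit the gap.

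**Stronger readings that the protocol does not support.**

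- A reader might infer that every patient lost to follow-up has the index-day value carried forward. That holds only for those with no later EHR reading, and these are primary care patients in three health systems with data warehouses.
- A reader might take the 15% attrition rate as the share affected. Attrition there means neither a refill in the system nor a return for follow-up. Missing 6-month research readings could be more frequent, since phone or web follow-up gives none; patients without any later EHR reading could be fewer.
- A reader might charge the whole fall from 87% power (282.5 per cell, nobody lost) to 75% to the rule. At 15%, about 6 of those 12 points are ordinary attrition, which no data rule recovers.
- A reader might conclude that an immediate effect of the exercise would be reported as a sustained one. Section IV.G says "We also seek data on the potential for this social psychology intervention to have direct effect on blood pressure", but it does not mention a same-visit effect. The possibility cannot be excluded, but the protocol does not establish it.

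**Conclusion.** The point holds in a limited form. As written, the fallback can use an index-day, early or urgent-visit reading as the 6-month blood pressure, and this conflicts with the protocol's own index-against-6-month comparison. Only the supportive EHR-based analysis of a secondary outcome is affected.

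If 5%, 10% or 15% of values were replaced, a true 4.7 mmHg difference would appear as about 4.5, 4.2 or 4.0 mmHg, and power would be about 2, 4 or 6 points lower than if the same patients were left as missing. These figures assume that the replaced readings carry no 6-month effect, that the SD is about 18 mmHg (back-calculated), and that the shares are as chosen; the true share is unknown. Under these assumptions, adding such readings does worse than omitting them. The index-day part also rests on check-in readings being entered in the EHR and on the post-enrolment period including the index day, which the text does not settle.

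**What to change.** Amend the outcome definition in IV.A so that the EHR fallback:

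- excludes all readings from the index day;
- accepts only non-urgent outpatient readings, as time under control already does for its own readings;
- takes the reading within a pre-stated window around month 6. The bounds are the sponsor's choice; one example is the reading nearest day 180 and not before about day 90.

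Patients with no qualifying reading are treated as missing in the mixed model, in line with the approach already planned in IV.F.

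The cost is a sentence or two in the protocol and a date and visit-type filter in the data pull. The downside is a few more missing values in a supportive analysis.
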